## 6.0 Methodology

### 6.1 Study Design Overview

We propose to rigorously define and compare three widely adopted models for community-facility linkage with each other and the standard of care using a mixed methods approach involving both quantitative and qualitative data collection.

For the quantitative component, we will first use stratified random sampling to select facility catchment areas in 5 Malawi districts where implementing partners have focused PMTCT programming. We will then visit each selected area to construct a retrospective cohort of HIV-infected women who entered the national PMTCT program and received CFL services or the SOC between July 1, 2016 and June 30, 2017. These dates have been chosen to align with the latest change to Malawi HIV guidelines supporting universal “test and treat” strategy, which became national policy on April 1, 2016 and reached stable rolled out on July 1, 2016. Using existing data, we will gather individual-level retrospective data on each woman and her infant from PMTCT enrolment through the child’s second birthday. Next, we will enrich these data using an epidemiological sampling method designed to overcome the limitations traditionally associated with retrospective data (e.g. missing data, outcome misclassification, etc.). In this second stage, we will randomly select a sample of women from our full

cohort to create our nested cohort. These women will complete a questionnaire about their experiences with CFL models and services, undergo viral load testing, and have their children ages 12–24 months receive HIV testing. Such prospective data collection will enable us to confirm primary outcomes, fill in missing data, and improve study data quality more generally.

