## **7.2.2 Analysis Plan for Objective 2 & 2a**

### **7.2.2.1 Cohort Data**

We will calculate maternal retention in care as the proportion of mothers alive and in care at 6, 12, and 24 months post-ART initiation among all eligible women at the start of the cohort. We will also calculate median days from PMTCT enrolment to ART start to examine the effects of CFL models on time to ART initiation. We will look for differences in the delay of ART initiation across the CFL models and SOC using the Aalen-Johansen estimator to account for the competing event of death. We will report crude HEI mortality at 12 and 24 months as part of our survival analysis. We will define infant 12-month HIV free survival as the proportion of HEIs alive with a negative 12-month HIV-rapid test among all infants enrolled in the HEI birth cohort. Similarly, we will define infant 24-month HIV free survival as the proportion of HEIs alive with a negative 24-month HIV-rapid test among all infants enrolled in the HEI birth cohort. We will use Kaplan Meier techniques to compare infant HIV-free survival at 12 and 24 months across the 3 CFL models and SOC accounting for informative censoring and differences in baseline patient characteristics between the models using inverse probability weights. We will censor all survival outcomes on the last date of field activities in a given district (most likely between February 1, 2018 and April 30, 2019, depending on the district), the date of transfer, or the date of the last clinical encounter, as appropriate.

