#### *7.2.2.2 90-90-90 Virtual Survey Analysis*

Using data from the full retrospective cohort, enriched by nested cohort data, we will calculate HIV care cascade indicators for MIPs and compare results across CFL models/SOC according to established UNAIDS 90-90-90 definitions (i.e. 90% of women and infants know their HIV status; 90% of HIV-infected women and infants are sustained on ART; and 90% of women and infants on ART achieve viral suppression). The following 90-90-90 indicators will be calculated and presented together with their associated 95% confidence intervals (CIs):

Proportion of women who know their HIV status (i.e. “Known Maternal HIV status”): For this indicator examining the first step of the HIV care cascade (i.e. the “first 90”), we will define our denominator as the number of pregnant women with a recorded ANC or Maternity Department visit in the 12 months preceding the evaluation date (e.g. the last day of study activities in the targeted district). For the numerator, we will calculate the number of pregnant women with either a documented negative HIV test result in ANC or Maternity within the last 12 months (of the evaluation date) or documented positive HIV test/ evidence of being HIV-positive before the evaluation day (e.g. a women is known to be receiving ART).

Proportion of infants who know their HIV status (i.e. “Known Infant HIV status”): For this indicator, we will define our denominator as the number of HIV-exposed infants enrolled in the national HIV Care Clinic follow-up program or registered in the MOH EID testing logbook in the 12 months preceding the evaluation day (e.g. the last day of study activities in the targeted district). For the numerator, we will ascertain the number of infants with either a documented negative DNA PCR or rapid HIV test result within the last 12 months (of the evaluation date) or documented positive HIV test/ evidence of being HIV-positive before the day of evaluation (e.g. infant is known to be on ART).

Proportion of women receiving anti-retroviral therapy (i.e. “Maternal ART Initiation”): For this second step of the HIV care cascade (i.e. “the second 90”), we will calculate the proportion of HIV-infected pregnant and breastfeeding women initiating ART during the 12 months preceding the evaluation day among all PMTCT clients with a documented positive HIV test/ evidence of being HIV-positive before the day of evaluation.

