Proportion of infants/ young children receiving anti-retroviral therapy (i.e. “Infant ART Initiation”):

Similar to the related maternal indicator, for this infant ART initiation indicator, we will calculate the proportion of HIV-infected infants/ young children initiating ART during the 12 months preceding the evaluation day among all infants with a documented positive HIV test/ evidence of being HIV-positive before the day of evaluation.

Proportion of PMTCT mothers and infants/young children who started ART and have a suppressed HIV

viral load (“Viral suppression”): Using viral load test result data, we will calculate and present separately the proportion of ART-initiated, HIV-infected mothers and ART-initiated HIV-infected infants/ young children who achieved viral suppression. For this final step of the cascade (i.e. the “third 90”), we will use the numerators from the maternal and infant ART initiation indicators for our respective denominators, and will assess the subset of these denominators with documented suppressed viral load test results within 12 months of the evaluation day. We will define viral suppression using a number of established thresholds for HIV-1 viral load, including less than 20 copies/ ml (the lower limit of detection for VL testing performed on plasma collected by venipuncture), less than 550 copies/ml (the lower limit of detection for VL testing performed on DBS) and less than 1,000 copies/ml (the definition of viral suppression used in the recent MOH Malawi Population-Based HIV Impact Assessment).

*7.2.2.3 Maternal IDI Data*

For qualitative data, the same analytical approach will be employed as described for Objective 1 above, except that we will search for patterns in the data that help explain client experiences with CFL model services and navigating the PMTCT care continuum for mothers and their children.

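### The second 90 counts only ART starts in the 12 months before the evaluation day but divides by everyone known HIV-positive before it, so women who started earlier and are still on treatment count as not on ART

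*Protocol*

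**What the plan says.** Section 7.2.2.2 sets the source of the cascade: "Using data from the full retrospective cohort, enriched by nested cohort data, we will calculate HIV care cascade indicators for MIPs". The cohort is defined in section 6.1 as "HIV-infected women who entered the national PMTCT program and received CFL services or the SOC between July 1, 2016 and June 30, 2017".

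The maternal second 90 is the proportion of HIV-infected pregnant and breastfeeding "women initiating ART during the 12 months preceding the evaluation day among all PMTCT clients" with positive status documented before the evaluation day. The infant version has the same form: its numerator is infants and "young children initiating ART during the 12 months preceding the evaluation day", over all infants known to be infected before that day. For the third 90, "we will use the numerators from the maternal and infant ART initiation indicators for our respective denominators".

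The evaluation day is given only by example in section 7.2.2.2, as the last day of study activities in the district. Section 7.2.2.1 puts the last field date "most likely between February 1, 2018 and April 30, 2019, depending on the district". Section 6.5.2.2 instead expects administrative censoring between end 2017 and end 2018.

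The results are to be compared across models and with UNAIDS targets. Section 7.2.2.2 paraphrases the second target as 90% of infected women and infants being sustained on ART.

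**The concern.** Numerator and denominator run on different clocks. A woman leaves the numerator once her ART start is more than 12 months old, but she never leaves the denominator. Section 6.5.2.3.7 describes ART starting as soon as possible after diagnosis, so cohort starts should cluster near entry, between mid-2016 and mid-2017. The evaluation days fall from end 2017 to April 2019. In late-closing districts the look-back therefore begins after the whole cohort has entered.

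Three things are at stake:

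- The second 90 would fall short of its benchmark for a calendar reason, even if every woman started ART at entry and stayed on it.
- The third 90 would rest on the few women, or none, who started within the look-back. The viral loads of earlier starters, including those the study itself collects under section 6.5.2.3.5, would be left out of this indicator.
- The value depends on when a district closes, so comparisons between models could be distorted if closing dates differ by district.

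**Working it through.** The protocol gives no expected value for this indicator, only the 90% benchmark, so there is no figure to reproduce. The check is calendar arithmetic for mothers.

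**Inputs from the protocol**
- Entry window: 1 July 2016 to 30 June 2017, 365 days (6.1).
- Closing dates: 1 February 2018 to 30 April 2019 (7.2.2.1); end 2017 to end 2018 (6.5.2.2).
- As many as 15% of HIV-positive pregnant women do not start ART (2.0).

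**Assumptions not stated in the protocol**
- The evaluation day equals the district's last field day.
- Entry is uniform over the year.
- ART starts at entry (base case) or after an exponential delay with mean m days.
- Uptake is 100% unless stated.

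**Base case.** The share counted is the number of entry days on or after w, divided by 365, where w is the evaluation day minus 12 months.
- Close 31 Dec 2017: 31 Dec 2016 to 30 Jun 2017 is 182 days; 182/365 = 49.9%.
- Close 1 Feb 2018: 1 Feb to 30 Jun 2017 is 150 days; 150/365 = 41.1%.
- Close 30 Apr 2018: 62/365 = 17.0%.
- Close 30 Jun 2018: 1/365 = 0.3%.
- Close 1 Jul 2018 or later: 0/365 = 0%.

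**With delay to ART.** For a woman entering on day d with evaluation day E, the probability that her start falls in the look-back is A - exp(-(E - d)/m). Here A = 1 if d is on or after w, and A = exp(-(w - d)/m) otherwise. For example, with entry on 15 January 2017, E = 1 February 2018 and m = 30, w - d = 17 days, so the probability is exp(-17/30) = 0.57; the second term is negligible. Averaging over the 365 entry days:

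| Close | ART at entry | m = 30 | m = 60 | m = 90 | m = 180 |
|---|---|---|---|---|---|
| 31 Dec 2017 | 49.9% | 57.9% | 64.6% | 68.0% | 65.8% |
| 1 Feb 2018 | 41.1% | 49.2% | 56.5% | 61.2% | 62.4% |
| 1 Jul 2018 | 0% | 8.1% | 16.2% | 23.7% | 37.1% |
| 31 Dec 2018 | 0% | 0.0% | 0.8% | 3.1% | 13.4% |
| 30 Apr 2019 | 0% | 0.0% | 0.1% | 0.8% | 6.9% |

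**Other sensitivities, for closes on 31 December 2017 and 1 February 2018**
- 15% never starting: 0.85 × 49.9% = 42.4% and 0.85 × 41.1% = 34.9%. With a 30-day delay as well, 49.2% and 41.8%.
- Entry rate doubling over the year, ART at entry: 58.2% and 49.2%. Halving: 41.5% and 33.0%.

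The largest value in any of these scenarios is 68.0%. Section 6.3 also admits women with existing documented HIV infection. Any who were on ART before the look-back began can never enter the numerator, which pulls the value lower still.

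**With the look-back removed.** The ceiling is 100%, or 1 - 0.15 = 85% if 15% never start. Neither depends on the closing date.

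**The case against.** The evaluation day is introduced as an example, not fixed. Set at 30 June 2017, the look-back would coincide with the entry window and the loss among newly starting women would largely disappear. This stands to the extent that every figure above is conditional on the day. But the protocol offers no other day, and a definition that works only on a date it does not name needs correcting. If the population meant were wider than the cohort, the figures would change, but earlier starters still on ART would still be left out of the numerator.

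The reach is also limited. The primary outcome, 12-month maternal retention, does not use this indicator. Section 7.1 lists the proportion of clients initiated on ART as a secondary outcome with no look-back, and maternal viral suppression is a separate secondary outcome with its own methods in section 7.2.2.1. All of this stands: the damage is confined to the cascade analysis.

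Three stronger readings might be inferred, and the documents do not support them:

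- **That 41-50% is a hard ceiling.** It rests on uniform entry and same-day ART, neither of which is stated; a mean delay of 30 days already gives 58% at the earliest close.
- **That the maternal figures carry over to infants.** Women may enter at any gestational age up to 30 June 2017, so births run into early 2018, and testing continues from 6 weeks to 24 months or later. Infant ART starts can therefore fall well inside the look-back.
- **That bias between models is shown.** In Table 1, Salima and Neno are CHW-only and hold 11 of the 15 CHW sites, so the route for bias exists. But that table is illustrative, and no closing date is given for any single district. Neither direction nor size can be stated.

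**Conclusion.** The point holds as a defect in a stated definition. As written, the maternal and infant second 90 classify earlier starters who are still on ART as not on ART, and the third 90 loses the same people from its denominator.

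For mothers, with the evaluation day at district close, uniform entry and full uptake at entry, the second 90 would be about 50% at the earliest possible close (end 2017), 41% at the earliest close in section 7.2.2.1, and 0% from July 2018. Delays averaging 30 to 90 days raise the two early values to 58-68% and 49-61% and leave about 0-1% for a close on 30 April 2019. These are scenario values, but none comes near 90%, and the result is driven largely by closing date. The infant mismatch is structural and unquantified. Distortion of comparisons between models is possible, not demonstrated. The primary outcome and the ART-initiation secondary outcome in section 7.1 are not affected.

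**What to change.** In section 7.2.2.2:

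- Delete the 12-month look-back from the maternal and infant ART numerators, so that numerator and denominator cover the same cohort. Count those who started ART on or before the evaluation day, or by a common horizon from PMTCT entry (from diagnosis for infants), among all cohort members known to be HIV-positive.
- Use that group as the denominator of the third 90.
- Label the indicator ART initiation. If it is to be set against the target for being sustained on ART, define the numerator as on ART at the evaluation day, because a count of starts includes women who later stopped.
- Do not repair it by applying a rolling 12-month window to both parts. In districts closing from July 2018 no newly entered cohort woman would fall in the denominator, giving 0/0 in place of 0%.
- Reconcile the closing ranges in sections 6.5.2.2 and 7.2.2.1, and state the evaluation day outright.

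The cost is a change of wording. Section 6.6.3 already has ART start dates abstracted, so the initiation indicator needs no new data or participants.

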#### 6.4 Sample Size

After enumerating the full retrospective cohort, we will randomly select eligible HIV-positive women and their HEIs for our nested cohort. For this nested cohort, our sample size will be determined by a power calculation for our primary outcome of interest—maternal retention in care 12 months after ART initiation. For this calculation (*see summary in Table 2 below*), we assume that 75% of MIPs receive services from a CFL model of interest in our selected districts, and that approximately 73% of HIV-positive mothers receiving the SOC will be retained in care at 12 months post-ART initiation (based on the most recent, first quarter 2017 data from the Malawi national program). With a two-sided alpha of 0.05, we will have 80% power to detect a programmatically meaningful 8% difference in the proportion of mothers retained in care between those who do and do not receive CFL services by enrolling 894 mothers from CFL sites and 298 mothers from SOC sites into our nested cohort (for a total of 1,192 mothers). Assuming that approximately 75% of HIV-positive mothers in SOC sites will be virologically suppressed (a weighted composite of 88% suppression among the 73% of HIV-positive mothers in care and approximately 40% suppression among the 27% of HIV-positive mothers not in care), we will have 83% power to detect a 8% difference in the proportion of HIV-suppressed mothers between those who do and do not receive CFL services. Finally, assuming that we will enrol about one HEI for every mother in the nested cohort, and that 92% of all HEIs not receiving CFL services (i.e. receiving SOC) are alive and HIV-free at 12 months (based on published data that 7% of HEIs become HIV-infected by 12-months and 96% of HIV-exposed but *uninfected* infants are alive at 12 months), we will have 90%

power to detect a 5% difference in HIV-free survival between HEIs who do and do not receive CFL models of interest by recruiting 1,192 total HEIs..

| Table 2: Summary of power and sample size calculations for primary outcomes of interest. |                                 |                    |              |                                 |                                 |

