#### *6.5.2.3.7 Routine Care and Treatment for Maternal and Infant Nested Cohort Participants*

As we are proposing an observational study without intervention, routine HIV treatment and care for MIPs enrolled in the nested cohort will continue to be provided by MOH HCWs at MOH facilities according to standard clinical practice, in strict accordance with the Malawi Ministry of Health integrated PMTCT/ART guidelines.

Specifically, as part of routine clinical care, all pregnant women will receive the following standard services from the MOH per national guidelines: All pregnant women will receive HTS using the opt-out method at their first ANC visit. All pregnant women diagnosed with HIV infection will undergo ART education and counselling and confirmatory HIV testing prior to starting first-line regimen 5A

(TDF/3TC/EFV) as soon as possible. Women with a documented contraindication to 5A (e.g. renal failure or psychosis) will start an alternative regimen in accordance with national guidelines. Maternal prophylaxis will include cotrimoxazole (CPT) and isoniazid preventive therapy during pregnancy and thereafter per national guidelines. HIV RNA will be measured at 6 and 24 months post ART initiation, and every 2 years thereafter or in the event of clinical suspicion of treatment failure based on new WHO Stage 3 or 4 condition after more than 12 months on ART. Mothers will be seen monthly for 6 months after the initial ANC visit and then quarterly per Malawi HIV program recommendations.

As part of routine care provided by the MOH, all HEIs will be enrolled in the national HIV Care Clinic and will receive 12 once-monthly follow-up visits as detailed on the national pink card. HEIs will also receive nevirapine prophylaxis, CPT, HIV testing services, feeding counselling, and immunization services per national guidelines.

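### The third 90 in Protocol 7.2.2.2 counts ART starters with no viral-load result as unsuppressed, so it mixes testing coverage with suppression

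*Protocol*

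**What the plan says.** Section 7.2.2.2 announces the third 90 as "90% of women and infants on ART achieve viral suppression" and says that the cascade indicators will be compared across CFL models and SOC. Section 6.5.2.1 adds that they will be set against the 90-90-90 benchmarks. The data source is "Using data from the full retrospective cohort, enriched by nested cohort data, we will calculate HIV care cascade indicators".

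The operational definition follows. For the denominator, "we will use the numerators from the maternal and infant ART initiation indicators for our respective denominators". The maternal numerator so carried forward is women "initiating ART during the 12 months preceding the evaluation day among all PMTCT clients"; the infant rule is parallel. For the third-90 numerator the study "will assess the subset of these denominators with documented suppressed viral load test results within 12 months of the evaluation day". No rule is given for a starter without a result.

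Two other places bear on who has a result. Under routine care, "HIV RNA will be measured at 6 and 24 months post ART initiation" (6.5.2.3.7). Under 6.5.2.3.5, consenting nested-cohort participants on ART have blood drawn, with a study-specific sample if no recent result is on file. Section 7.2.2.1 states, for all estimates, a correction based on the sampled pairs, using weights for site sampling, individual sampling and participation.

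**The concern.** A person with no result stays in the denominator and can never reach the numerator. The printed ratio is therefore not the quantity that the same section says it wants. It falls when fewer viral loads are drawn or filed, even if nobody's viral load changes.

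A uniform shortfall would distort only the reading against 90%. The harder problem is the comparison between models. Drawing and documenting viral loads is something that community support may itself change. In addition, the study tests its own nested participants, and the nested fraction of the cohort is far from equal across models. A ranking on this indicator could therefore reflect who was tested. The results go to policy makers and programme managers (8.1), who would read the figure as suppression.

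**Working it through.** **The plan's own figure.** Section 6.4 assumes that "approximately 75% of HIV-positive mothers in SOC sites will be virologically suppressed", built from 88% among the 73% in care and 40% among the 27% not in care: 0.88 × 0.73 + 0.40 × 0.27 = 0.6424 + 0.1080 = 0.7504. This reproduces 75%. It covers all SOC mothers, in and out of care, so it is used below only for scale, with 88% as a higher alternative.

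**What the printed rule computes.** Let N be the ART starters, T those with an in-window result, and S those with a suppressed result. Then S/N = (T/N) × (S/T) = c × s, where c is coverage and s is suppression among those tested. The protocol gives no value for c, so every c below is an assumption.

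**Level.**
- With s = 0.75, the indicator reads 0.375, 0.525 and 0.675 at c = 0.5, 0.7 and 0.9.
- With s = 0.95, it reaches 0.90 only if c is at least 0.90/0.95 = 0.947.

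**Comparison.** With equal s in two models, the false difference is s × (difference in c). A 10-point coverage gap gives 0.75 × 0.10 = 7.5 points, or 0.88 × 0.10 = 8.8 points. Section 6.4 plans to detect an 8-point difference in suppression.

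**Nested share by model.** These are Table 3 counts, with strata assigned to models by Table 1:

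| Model | Strata | Sampled | Available | Share |
|---|---|---|---|---|
| SOC | 5, 9, 17 | 180 | 230-320 | 56-78% |
| Mentor mother | 6, 10, 18 | 300 | 650-900 | 33-46% |
| Expert client | 7, 11, 19 | 330 | 1,350-1,700 | 19-24% |
| CHW | 4, 8, 16, 20 | 390 | 510-800 | 49-76% |

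The columns sum to the printed totals of 1,200 and 2,740-3,720. In strata 10 and 16 the sampled number exceeds the low end of the available range, so the upper shares for mentor mother and CHW are rough.

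**Illustration.** Suppose that all nested women are tested, routine coverage is 50% in every model, s = 0.75 everywhere, and the data are pooled without weights. Then c = f + (1 − f) × 0.5, where f is the nested share, and the indicator is 0.75 × c:
- Expert client: c = 0.597-0.622, indicator 45-47%.
- Mentor mother: c = 0.667-0.731, indicator 50-55%.
- SOC: c = 0.781-0.891, indicator 59-67%.
- CHW: c = 0.744-0.882, indicator 56-66%.

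CHW exceeds expert client by 9 to 21 points (55.8 − 46.7 to 66.2 − 44.8) although suppression and routine testing are identical. This uses whole-cohort shares. The shares within the 12-month ART-start window cannot be derived from the protocol.

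**Dropping the untested is not neutral either.** Suppose that only in-care SOC mothers have a result. On 6.4's figures the printed rule then gives 0.73 × 0.88 = 64.2%, a tested-only ratio gives 88%, and the assumed truth is 75.0%.

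**The window.** Cohort entry runs from 1 July 2016 to 30 June 2017 (6.1). The evaluation day is, for example, the last day of study activities in the district, and 7.2.2.1 expects field activities to end between 1 February 2018 and 30 April 2019. At the earliest date, the 12-month window reaches back to February 2017 and overlaps the last five months of entry. After 30 June 2018 it overlaps none of the entry period, and at the latest date it opens about ten months after entry closed. For mothers, the denominator would then hold only late starters.

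**The case against.** The strongest reply is that the protocol already contains the cure. Section 7.2.2.1 says that all estimates are corrected to the sampled pairs, the abstract says that full-cohort estimates will be revised from the nested results, and nested participants on ART are tested. A weighted nested estimate with near-complete testing would lose most of the shortfall, and the unweighted illustration would not apply. This reply has real force and limits the point. It does not dispose of it: the weighting sentence stands in the preceding subsection, 7.2.2.2 names the full cohort as its data source, and nothing there ties the third 90 to the weighted nested sample. The participation weight also does not cover a participant who has no viral-load result.

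It can also be said that the numerator is openly labelled as documented results, and that the effect of CFL services on maternal suppression is analysed separately in 7.2.2.1 by survival methods allowing for interval censoring. Both are true. That separate analysis is not affected.

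A reader might infer more than the text supports:
- That women 18-24 months after ART start can never count as suppressed, because their routine tests fall outside the window. Read as written, the denominator holds only ART starts in the 12 months before evaluation, so these women are not in it.
- That 7.2.2.2 contradicts a definition of suppression in 6.4 or 7.1. Section 6.4 gives planning assumptions and 7.1 names an outcome. The copies/ml thresholds stand only in 7.2.2.2.
- That the indicator measures nothing but testing. It is a product, and approaches true suppression as coverage approaches 100%.

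**Conclusion.** The point holds in limited form. As written, the third 90 is coverage times suppression among the tested. It understates suppression whenever coverage is incomplete, and it misleads between models whenever coverage differs. The algebra needs no assumption; the size does. At 75% suppression, each 10 points of coverage gap produces 7.5 points, about the difference that the study was planned to detect. The 9-to-21-point CHW-expert client gap additionally assumes unweighted pooling, 50% routine coverage and whole-cohort nested shares, so it shows what the wording permits and is not a forecast. If the indicator is in fact computed from the weighted nested cohort with nearly everyone tested, little of this remains, but the section has to say so. The mismatch between the ART-start window and the cohort dates needs resolving in either case. This is a secondary cascade indicator; the primary retention outcome is untouched.

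**What to change.** Reword the third-90 paragraph of 7.2.2.2:
- Estimate it from the nested cohort among ART starters, using a study viral load or a routine result within the window, with the sampling and participation weights of 7.2.2.1.
- Add weighting for ART starters in the nested cohort who have no result, rather than dropping them or counting them as unsuppressed.
- Report viral-load coverage (any in-window result divided by ART starters) by model as an indicator of its own.
- Keep the all-starters ratio only as a labelled lower bound.
- Reconcile the 12-month ART-start window with the July 2016 to June 2017 cohort and with field activities that may end as late as April 2019.

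No new data are needed. There are two costs. The confidence interval widens, because the estimate rests on about 1,200 pairs rather than the full cohort. There may also be upward bias if people who stopped ART have no result, since 6.5.2.3.5 provides viral-load testing for participants on ART. The extra weighting reduces that bias to the extent that measured covariates explain who lacks a result, and the lower bound shows how much could be at stake.
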